### Outcome measurements

#### Primary outcome

The number of migraine attacks during weeks 11 to 14 from randomisation, as recorded in the participant diary, with an attack being defined as in the IHS International Classification of Headache Disorders [10].

#### Secondary outcomes

##### Efficacy

1. **Response**, defined as a 50% or greater reduction in number of attacks during weeks 11 to 14; 25 to 28; 37 to 40, relative to baseline, as recorded in the participant diary.

2. **Headache intensity; **headache intensity will be measured on the standard 4 point scale [10]. As migraine headache is usually moderate or severe (with additional features), mild headaches will not be recorded, unless they are associated with sufficient additional features to meet the diagnostic criteria for migraine attack. Headache intensity as experienced during the worst part of the migraine attack will be averaged during weeks 11 to 14 for each participant.

3. **Use of rescue medication**, defined as the number of rescue doses taken during weeks 11 to 14, as recorded in the participant diary.

4. **School attendance**, defined as % of school half days attended during weeks 11 to 14, as recorded by diary.

5. **Recalled Attack Frequency**: participants reply at visit 6 to "How many migraine attacks did you have in the 4 week assessment block (weeks 11 to 14)?" They may discuss with their parents/guardian and look at their diary if they wish. This will help in imputing missing values for those who can provide no diary information.

6. Quality of life & functional outcomes using:

6.1 the health-related quality of life tool PedMIDAS;

6.2 the non-health-related Generic Child Quality of Life measure GCQ.

##### Health Economics

Sufficient data to allow cost effectiveness comparisons from NHS and family perspectives will be collected but not analysed at this stage. If one or other active treatments proves effective in comparison to placebo, then separate funding for a formal cost comparison and cost effectiveness study will be sought.

1. Parent's/guardian's time off work mainly related to child's migraine, for those in full time paid employment, or pro-rata for those in part-time paid employment, during weeks 11 to 14, as recorded in the participant diary.

2. Costs of Propranolol, Pizotifen, and placebo (study medications)

3. Cost of rescue medications

4. Number and length of emergency hospital admissions and Emergency Department attendances, and non-trial hospital and GP surgery appointments, related to migraine, with dates and place will be recorded in the participant diaries so the cost of investigations can be determined later

5. Cost of "child half days off school" (4 above)

6. EQ-5D for parents/guardian and participants aged 12-16 years; UK Proxy EQ-5D for younger participants.

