### Interventions

#### Propranolol

A non-selective beta-blocker which crosses the blood-brain barrier exerting central as well as peripheral effects and which has been used in migraine prevention since the 1960s [5]. It is generally well tolerated but in high dose can be associated with fatigue or sleep disturbance. It can also cause bronchospasm and exacerbate asthma.

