#### Secondary hypotheses

• To test whether any therapeutic effect out lasts the period of drug administration.

• To test whether a dose (in mg/kg/day) - response relationship exists at the doses used.

• To test whether active treatment improves participation by school attendance, and parent/guardian time off work, and health related and non-health related quality of life, and health status.

• To estimate cost-effectiveness if either active treatment proves superior to placebo.

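### Contacts and parental time off are recorded for costing only if related to migraine, so use caused by drug side effects is left out and a later cost comparison is likely to favour the active drugs

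*Protocol article*

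**What the plan says.** The Secondary hypotheses of the protocol article include an economic aim: "To estimate cost-effectiveness if either active treatment proves superior to placebo". The opening of the Health Economics section says how it will be served: "Sufficient data to allow cost effectiveness comparisons from NHS and family perspectives will be collected but not analysed at this stage". A formal cost study is to follow if a drug proves effective and separate funding is found.

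Two of the listed items carry a restriction by cause:

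- Item 4, health care use: after the number and length of emergency admissions and emergency department attendances, the list continues "non-trial hospital and GP surgery appointments, related to migraine, with dates and place will be recorded in the participant diaries".
- Item 1, parental work loss: "time off work mainly related to child's migraine, for those in full time paid employment", or pro rata for part-time work, in weeks 11 to 14.

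Two other items carry no such restriction. Item 5 costs school half days, which the Secondary outcomes section defines by attendance whatever the reason for absence. Item 6 is EQ-5D (proxy version for younger children), a general health measure.

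The Interventions section names side effects of both drugs. For propranolol it mentions fatigue and sleep disturbance at high dose, and adds: "It can also cause bronchospasm and exacerbate asthma". For pizotifen it mentions drowsiness, increased appetite and weight gain.

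**The concern.** A cost comparison of a drug with placebo has to weigh care avoided because attacks are fewer against care caused by the drug. Items 1 and 4 collect the first and leave out the second. A GP visit for daytime tiredness or weight gain, or a parent's day at home because of it, is not naturally an event related to migraine, so a family following the diary wording would not enter it.

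The named side effects belong to the active drugs, so the omission is expected to fall more heavily on the active arms. The promise of sufficient data from both perspectives is then not met by the items listed under it. Because the economic analysis is deferred, the later study can choose its own model, but it probably could not recover routine contacts and lost workdays that nobody wrote down at the time.

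**Working it through.** The article states no figure on this point, so there is none to reproduce. The check has two parts.

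**1. Which listed item would capture a consequence of a side effect?**

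| Consequence of a side effect | Where it could be captured | Captured? |
|---|---|---|
| Non-trial GP or hospital appointment | Health Economics item 4 | No, limited to migraine |
| Emergency admission or emergency department attendance | Health Economics item 4 | Unclear: the qualifier may govern the whole list or only the appointments |
| Parental time off work | Health Economics item 1 | No, must be mainly related to migraine |
| School absence | Item 5, from the school attendance outcome | Yes, all causes, weeks 11 to 14 |
| Loss of health status | Item 6, EQ-5D | Yes |
| The event itself | Adverse events sections | Yes, with severity and relationship; no contacts, length of stay or work loss are mentioned |

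The gap is therefore non-trial appointments and parental time off, and perhaps admissions and emergency attendances.

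**2. Direction and possible size.**

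Let *a* and *p* be the side-effect contacts per child on active drug and on placebo, and *c* the cost per contact.

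Error in recorded incremental cost (active minus placebo) = −(*a* − *p*) × *c*

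If *a* > *p*, incremental cost is understated. If *a* = *p*, the error is zero. If *a* < *p*, it reverses. The article gives none of *a*, *p* and *c*. With an assumed excess *a* − *p* of 0 to 0.15, unrecorded contacts per 100 children on active drug are 100 × 0 = 0 to 100 × 0.15 = 15, and incremental cost is understated by 0 to 0.15 × *c* per child.

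To judge whether that could matter beside the saving that is recorded, assume further that placebo children have 0.10 to 0.20 migraine-related contacts each over the 16 weeks on trial medication (2 + 12 + 2 weeks, Follow up procedures). Assume also that contacts fall by the 33% that the Sample size section assumes for attacks. The recorded saving is then 0.10 × 0.33 = 0.033 to 0.20 × 0.33 = 0.066 contacts per child. The true net saving is this minus the excess:

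| Assumed excess *a* − *p* | Net contacts saved per child |
|---|---|
| 0 | +0.033 to +0.066 |
| 0.03 | +0.003 to +0.036 |
| 0.05 | −0.017 to +0.016 |
| 0.10 | −0.067 to −0.034 |
| 0.15 | −0.117 to −0.084 |

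The sign depends wholly on the assumed excess: up to 0.03 the saving stands, at 0.05 it may go either way, and from 0.10 it becomes extra use. The table counts every contact alike, although an admission costs far more than a GP visit. It shows only that the omission could be of the same order as the saving.

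**The case against.** A reader might infer that any cost comparison from these data must favour the active drugs, or that the recorded saving would really be extra use. The article supports neither. It gives no rates or unit costs, and the table above shows a genuine saving at low excess rates.

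There are reasons to expect a low excess. Both drugs are described as generally well tolerated, and propranolol's fatigue and sleep disturbance are tied to high doses. Pizotifen is given at bedtime to avoid sleepiness. The first exclusion criterion removes children with asthma, bronchospasm or wheeze in the last 12 months or on daily asthma prevention, which weakens the bronchospasm example. Research nurses visit at home and keep in close telephone contact, so mild complaints may never reach a non-trial appointment. All of this stands as a limit on size. It does not make the excess zero, and the exclusions do nothing about drowsiness, fatigue or weight gain.

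A reader might also infer that side effects are wholly absent from the economic data. They are not: EQ-5D and school half days reflect part of their burden. Nor is the all-cause school measure a contradiction of items 1 and 4. It is an efficacy outcome reused for costing, and measures may differ in scope.

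Finally, this is a condensed article. The full protocol may log contacts on the adverse event form, and condition-specific costing is a recognised choice. But the restriction in items 1 and 4 is stated, not merely undescribed, and it stands beside an explicit promise of sufficient data.

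**Conclusion.** The point holds in a limited form. Items 1 and 4 restrict parental time off and non-trial appointments (on one reading, also admissions and emergency attendances) to those related to migraine. No other listed cost item covers the contacts or work loss caused by the side effects that the article names. If side-effect care is more frequent on active drug than on placebo, which is likely but not shown, incremental cost is understated and the later comparison leans towards the active drugs.

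The amount cannot be determined from the article. The range of 0 to 15 unrecorded contacts per 100 children on active drug rests on an assumed excess, and a change of sign in the cost comparison is a possibility, not a finding. The effect is confined to an economic study that depends on proven efficacy and separate funding. The primary outcome and the efficacy and safety analyses are untouched. The change is still worth making because it is cheap and the missing data probably could not be recovered later.

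**What to change.** In Health Economics items 1 and 4, record all non-trial appointments, admissions, emergency department attendances and parental time off work for the child's health, from the start of trial treatment. Add a tick box for the reason: migraine, possible side effect of trial medication, or other. This also settles whether the present qualifier applies to admissions and emergency attendances.

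Keep weeks 11 to 14 as a reported window for item 1. State that the cost comparison will be based on migraine plus possible side-effect use, with the migraine-only and all-cause totals shown as separate lines. The all-cause line matters because families have to judge the reason while blinded and will sometimes misjudge it.

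The cost is a change of diary and protocol wording, a few more diary entries, and somewhat noisier cost data.

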#### Adverse events

Safety and tolerability variables

These include:

1. Adverse Event (AE) reports:

a) spontaneous,

b) elicited by routine enquiry using the AE check list,

c) findings from physical and neurological examinations

2. Vital signs: Blood Pressure, Heart Rate, Weight and Height.

3. Participant's wish to continue (or parent/guardian's where child unsure) with allocated trial medication after week 14.

4. Time until withdrawal from allocated trial medication, from randomisation to end of week 14. Reasons for withdrawal will be recorded in CRF.

#### Follow up procedures

Participants in all three groups will follow the same schedule of study visits up to the end of the trial, regardless of their compliance with the trial medication. Screening & baseline assessments will be performed during visits 1-3, with a 4 week "run-in" ending in randomisation at visit 2 and start of trial treatment at visit 3. Visits 4-6 will take place during the 2 week dose escalation period, 12 week maintenance and 2 week down-titration phases. Visits 7 & 8 will take place during a 3 month blinded off-treatment phase, visit 9 during a 3 month unblinded follow-up with visit 10 marking the end of the Trial, at which point there will be an option to consent for a possible future follow-up study, (Figure 1).

**Figure 1 F1:**
[figure not shown]
**Patient and family involvement over time**.

#### Data Monitoring Committee (DMC)

An independent Data Monitoring Committee (DMC) will evaluate the outcome and safety data in the context of the overall trial and the currently existing information about the study drugs. No formal interim analyses for efficacy are planned. For these "administrative" analyses, informal Haybittle-Peto type boundaries [17,18] will be adopted for efficacy to permit the DMC to break the blind if it wishes, with negligible effect on the properties of the final analysis

#### Types of Analyses

The primary efficacy parameter will be the relative attack rate between the two treatment arms and their placebo arms, estimated by a Poisson regression model. The model will include terms to account for treatment arm, stratification variables and other covariates (baseline frequency of attacks, prior Triptan use and whether treatment naïve). The anticipated over- dispersion will be accounted for by estimation of robust standard errors.

The analysis will be performed on the full analysis set (following the intention to treat principle). For the primary efficacy analysis the statistical test will be two-sided at a nominal 5% two-sided significance level (see sample size justification).

##### Secondary outcomes

All secondary endpoints will be analysed using analysis of covariance, logistic regression or Poisson regression as appropriate. Secondary analyses will include a repeated measures analysis of the attack frequency at different time points (11-14 weeks; 25-28 weeks; 37-40 weeks from randomisation). Headache frequency will also be analysed with respect to the mean mg/kg/day dose for the active treatments for each participant during this period.

Again, terms to account for treatment arm, stratification variables and covariates will be included in the model with allowance for over-dispersion of binary/count data. Time to event data will be handled by survival regression. All secondary endpoints will be analysed only in the full analysis set.

For the secondary analyses (excluding cost analyses), tests and confidence intervals will also be two-sided and performed at the 5% significance level. No adjustment for multiple testing will be performed.

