### Randomisation and blinding

The randomisation will be based on a computer generated pseudo-random code using random permuted blocks of randomly varying size, created by the Nottingham Clinical Trials Unit (CTU) in accordance with their standard operating procedure (SOP) and held on a secure server. The randomisation proceeds in two stages: firstly a randomisation to one trial or the other; secondly a randomisation within each trial to active or placebo arm. The randomisation within each trial will be stratified by age (5-11 years *vs *12-16 years), type of migraine (two categories) and recruiting centre (10 centres).

Investigators will access the treatment allocation for each participant by means of a remote, internet-based randomisation system developed and maintained by the Nottingham CTU. The sequence of treatment allocations will be concealed until interventions have all been assigned and recruitment, data collection, and all other trial-related assessments are complete.

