## Discussion

The protocol design posed some particular challenges. The funding brief was for a 3 arm trial of Propranolol, Pizotifen, and Placebo. For statistical and operational reasons we are technically undertaking 2 parallel 2-arm trials, but blinding will make it indistinguishable to participants and local investigators from a 3 arm trial. This way if there is a problem with one trial the other can continue un-hindered.

We undertook several consumer involvement exercises, with help from the Medicines for Children Research Network (MCRN), and it was clear that keeping participants and their parents/guardians blinded for up to 2 years after their participation was not acceptable and could present a significant barrier to recruitment and retention. Participants and their families were content to be blinded during the trial treatment phase, but wanted to know what the treatment had been as soon as possible afterwards, to inform future treatment decisions. We were keen to maintain the blinding for as long as possible to avoid investigators being biased in their approach to potential participants, e.g. by being biased by preliminary results against one of the active treatments. Also we felt that the long-term assessments would be compromised if they were undertaken unblinded. As a compromise, and taking note of consumers concerns, we decided to unblind at visit 8 (week 29/30) see Figure 1. Consumers at the focus group were supportive of this delay in unblinding.

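### Attack counts and response at weeks 37-40 are analysed on the same footing as the blinded blocks, although allocation is disclosed at week 29/30

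*Protocol article*

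**What the plan says.** One secondary hypothesis in the protocol article is "To test whether any therapeutic effect out lasts the period of drug administration". Two parts of the plan bear on it. Under the secondary efficacy outcomes, response is defined as "a 50% or greater reduction in number of attacks during weeks 11 to 14; 25 to 28; 37 to 40, relative to baseline". Under Types of Analyses, the subsection on secondary outcomes states: "Secondary analyses will include a repeated measures analysis of the attack frequency at different time points (11-14 weeks; 25-28 weeks; 37-40 weeks from randomisation". The same subsection sets two-sided tests at 5% with no multiplicity adjustment. Neither place distinguishes the blocks by blinding.

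Attacks are counted "as recorded in the participant diary, with an attack being defined as in the IHS International Classification of Headache Disorders".

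Follow up procedures describes 2 weeks of escalation, 12 of maintenance and 2 of down-titration, then three months off treatment and blinded, then three months unblinded. The Discussion gives the timing: "we decided to unblind at visit 8 (week 29/30". It also says "we felt that the long-term assessments would be compromised if they were undertaken unblinded", and reports that families wanted to learn their allocation so that it could guide later treatment. Randomisation and blinding says: "The sequence of treatment allocations will be concealed until interventions have all been assigned and recruitment, data collection, and all other trial-related assessments are complete".

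**The concern.** The last block is collected when family and investigator know what the child received, and the outcome is a count that the family records. Knowing the allocation can change what is recorded. It can also change what treatment the child takes next, which is the purpose for which families asked to be told. Both can differ by arm, and both arise after randomisation, so analysing everyone as randomised does not remove them.

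The result at stake is the answer to the carry-over hypothesis. If weeks 37-40 feed that answer on equal terms with weeks 25-28, an arm difference could be read as a lasting drug effect when it partly reflects disclosure. A real lasting effect could equally be hidden.

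**Working it through.** **Timeline, from Follow up procedures, Success of blinding and the Discussion**

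- Trial treatment lasts 2 + 12 + 2 = 16 weeks. Maintenance ends at 2 + 12 = week 14, so weeks 11-14 are its last four weeks.
- Disclosure is at week 29/30, so weeks 37-40 start 37 − 30 = 7 to 37 − 29 = 8 weeks later.

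| Block | Trial drug | Allocation known to family and investigator |
|---|---|---|
| Weeks 11-14 | On | No |
| Weeks 25-28 | Off | No |
| Weeks 37-40 | Course finished; the phase is labelled only as unblinded | Yes |

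The section on permitted medication holds the dose of other preventives constant only during the 12-week assessment. Nothing in the article limits changes between disclosure and week 37.

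**Illustration of size**

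The plan gives no figure on this point, so none can be reproduced. The following only shows how sensitive a 5% test would be.

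Inputs from Sample size:
- mean 3 and variance 4, so over-dispersion is 4/3 = 1.33;
- 226 evaluable per trial at 2:1, so about 75 placebo and 151 active;
- 2 to 3 attacks per block (μ).

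The 226 is taken as stated. A standard events formula with a rate ratio of 0.667 gives 215 events, and 215/2.5 × 1.33 = 114. That mismatch is a separate matter and does not affect this point.

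Assumptions not in the document: no true carry-over; disclosure multiplies reported attacks in the active arm, relative to placebo, by b at weeks 37-40; all 226 are still evaluable then; within-person correlation ρ between blocks is 0.3 to 0.6.

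For weeks 37-40 alone:

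- SE = √(1.33 × [1/(75μ) + 1/(151μb)])
- P(p < 0.05) = Φ(−ln b/SE − 1.96) + Φ(ln b/SE − 1.96)

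With b = 0.90 and μ = 3: SE = √(1.33 × [1/225 + 1/407.7]) = 0.096; 0.105/0.096 = 1.10; P = 0.196. With μ = 2: SE = 0.117; 0.105/0.117 = 0.90; P = 0.146.

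For the average of weeks 25-28 and 37-40, the shift halves and the SE is multiplied by √((1 + ρ)/2).

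| Assumed shift favouring active | Weeks 37-40 alone | Average of 25-28 and 37-40 |
|---|---|---|
| None | 5% | 5% |
| 5% | 7-8% | 6% |
| 10% | 15-20% | 8-11% |
| 15% | 28-39% | 12-18% |
| 20% | 46-63% | 18-29% |

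The ranges cover μ from 2 to 3 and, in the last column, ρ from 0.3 to 0.6. Weeks 25-28 alone stay at 5%, because allocation is not yet known. A shift in the other direction would mask a true lasting effect.

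**The case against.** Disclosure at week 29/30 is a deliberate and openly stated compromise. The remark that unblinded long-term assessment would be compromised is given as the reason for delaying disclosure, and the delay is what keeps weeks 25-28 blinded. The final phase is plainly labelled as unblinded. All of this stands. The point is not that disclosure is wrong, but that its consequence is not carried into the analysis text.

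Several stronger readings are tempting, and the document does not support them:

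- A reader might infer that one arm effect will be averaged over all three blocks. With a 33% effect on drug and none afterwards, that average would be exp(ln(0.667)/3) = 0.87, which describes no period. The article does not say such an average will be reported. Effects by time point are a natural reading, and model terms are commonly left to the analysis plan.
- A reader might conclude that the trial cannot test for a lasting effect. It can: weeks 25-28 are off trial drug, blinded and already collected. The hypothesis is not tied to weeks 37-40.
- A reader might see a flat contradiction between the concealment sentence and disclosure at visit 8. That sentence can be read as covering only the master sequence, so it is unclear rather than necessarily wrong.
- A reader might treat weeks 37-40 as simply off drug. The article uses that label only for the blinded phase.

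**Conclusion.** The concern holds in a limited form. The plan gives an unblinded, diary-based block the same standing as two blinded ones in tested secondary analyses. The protocol's own Discussion supplies the reasons why that block is weaker. The arm contrast at weeks 37-40, and any estimate that pools it with weeks 25-28, may combine carry-over, knowledge of allocation and later treatment.

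The timeline is certain from the text. The size and direction of bias are not. The percentages in the working rest on assumed shifts in one direction only and should not be quoted as expected error rates. For example, families from the placebo arm might start another preventive once told, which would work against the active arm.

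The primary outcome at weeks 11-14 is untouched. This is a cheap improvement to secondary analyses, not a threat to the trial. It also does not justify discarding the weeks 37-40 data.

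**What to change.** 1. Name the arm contrast at weeks 25-28 (off trial drug, still blinded) as the test of whether an effect outlasts treatment.
2. In the repeated-measures model, include arm-by-period terms, report the arm effect for each period, and base no conclusion on an effect pooled over blocks.
3. Report attack counts and response at weeks 37-40 separately, labelled as unblinded and supportive, and describe by arm the preventive treatment started after disclosure.
4. Reword the concealment sentence under Randomisation and blinding so that keeping the sequence concealed is consistent with releasing individual allocations at visit 8.

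The cost is a change of wording and analysis only, with no change to visits, data collection or sample size. The downside is that weeks 37-40 lose equal standing as a tested secondary time point.

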#### Placebo

Both liquid and tablet formulations of the placebo will be manufactured using the same excipients used in the active formulation of the drugs minus the active ingredients. The placebo, Propranolol and Pizotifen tablets are matched in appearance; the liquid placebo matches the liquid Propranolol in appearance and taste but the liquid Pizotifen has a slightly different flavour.

All participants will be offered a choice of liquid or tablet preparations of the trial treatments. Because Pizotifen only has an evening dose, while Propranolol is given twice daily, to maintain blinding participants in the Propranolol and placebo arms will receive morning and evening doses from separate bottles; those in Pizotifen arm will take a morning placebo dose and an active evening dose (also from separate bottles).

For both active arms in this trial, starting, titration and age specific maintenance doses are consistent with the recommendations in "Medicines for Children" [6] and the new "British National Formulary (BNF) for children" [7] for 80% of participants by standard growth charts for the tablet preparations. The maximum dose of the liquid preparation is less to comply with World Health Organisation (WHO) recommendations on maximum intake of propylene glycol (used as a preservative for the liquid preparation of Propranolol).

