We were keen to develop a protocol particularly suited to children and young people. In contrast to adult participants, they often express fear and avoidance of medical settings and procedures, although they are usually curious and supportive of clinical research in general and are often remarkably altruistic. With this in mind we minimised the invasive procedures commonly undertaken in trials: there are no blood tests and only routine out-patient procedures. Most contacts with the participants will be by home visits by research nurses, or by phone call, with hospital visits approximately every 3 months, so that approximately 1 additional visit over the year is anticipated. We needed a liquid formulation, as younger children would be unable to swallow tablets. However, we decided to offer participants the choice of liquid *or *tablets as our consumer involvement work suggested that many young people of secondary school age (teenagers) did not want to take liquid preparations, and that would prove a barrier to recruitment. Tablet and liquid formulation concentrations were such that the numbers of tablets taken were the same for Propranolol, Pizotifen, placebo, during titration, maintenance and withdrawal, phases as were the volumes of liquid formulations.

Being able to offer participants tablets also mitigates the problem posed by the maximum ceiling dose caused by the propylene glycol (see "interventions section above) in the Propranolol liquid. We anticipate that most participants will take tablets because migraine is more common in secondary school aged young people than younger children.

We considered blinding essential in this definitive study, and ideally wanted full blinding of participants, their parents/guardian, their paediatrician/local investigator and research nurse, and trial statistician, for which trial the participants were in (Propranolol, or Pizotifen), as well as within each trial (active *vs *placebo). To avoid sleepiness commonly seen with Pizotifen we decided that Pizotifen would only be given at bedtime (which is frequent routine clinical practice), and to keep the blind a placebo dose is given in the mornings. Families therefore are given a supply of morning doses as well as a supply of evening doses, and the importance of using the correct supply at the correct time will be emphasised by the research nurses.

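### The planned dose-response test uses mg/kg/day, which is not randomised, and the listed model terms omit weight, formulation and age within band

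*Protocol article*

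**What the plan says.** The secondary hypotheses of the protocol article include "To test whether a dose (in mg/kg/day) - response relationship exists at the doses used". The secondary-outcomes paragraph under Types of Analyses gives the method: "Headache frequency will also be analysed with respect to the mean mg/kg/day dose for the active treatments for each participant during this period". The next paragraph puts treatment arm, the stratification variables and covariates into the secondary models. It sets tests at two-sided 5% with no multiplicity adjustment.

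The stratification variables are age (5-11 against 12-16 years), migraine type and centre (Randomisation and blinding). The covariates are baseline attack frequency, prior triptan use and whether the child is treatment naive (Types of Analyses).

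Three statements describe how dose arises. The interventions text says that "starting, titration and age specific maintenance doses are consistent with the recommendations". It also says "All participants will be offered a choice of liquid or tablet preparations of the trial treatments" and "The maximum dose of the liquid preparation is less to comply with World Health Organisation (WHO) recommendations on maximum intake of propylene glycol". The Discussion adds "We needed a liquid formulation, as younger children would be unable to swallow tablets". On matching across arms it says: "the numbers of tablets taken were the same for Propranolol, Pizotifen, placebo, during titration, maintenance and withdrawal, phases as were the volumes of liquid formulations".

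**The concern.** Children are randomised to one of the two trials and then to active or placebo. Nobody is randomised to a dose level. Among treated children, mg/kg/day therefore differs because the children differ in age, weight and chosen formulation, and in doses missed if the mean is taken over doses actually swallowed. Of these, the listed terms cover only age, and only in two bands.

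If heavier or older children within a band have more attacks, they also receive fewer mg/kg. The model would then show fewer attacks at higher mg/kg even if dose had no effect. A listed hypothesis, worded as a test at an unadjusted 5%, could then support a false statement about dosing per kilogram in children.

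**Working it through.** The plan gives no power, effect size or sample size for this analysis, so there is no figure to reproduce. The check has an algebraic part and an illustration.

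**1. What drives mg/kg/day.** log(mg/kg) = log(dose) - log(weight). If dose is fixed by age band and formulation, then within a given band and formulation log(dose) is constant. The slope on log(mg/kg) is there exactly minus the slope on log(weight).

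**2. How much the age band removes.** Assumed, because the dosing table is not shown: ages uniform over 5-17; mean weight 18 + 3.6 × (age - 5) kg with about 18% spread; dose doubling at 12; liquid at 0.8 of the tablet dose, taken by 60% of younger and 15% of older children; full compliance. Age band alone explains about 14% of the variance of log(mg/kg). Age band, formulation and log weight together explain 100%. The planned term thus leaves about 86%. Adding all the missing terms to an active-only model would leave no independent dose variation except from compliance or individual titration.

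**3. False rejection when age is prognostic.** Same set-up with 300 children per trial (half of the 600 target), 2:1, no dose effect, rate ratio 2/3 and 600 runs per setting. Sample size gives mean 3 and variance 4, so a gamma-Poisson with variance μ + μ²/k needs 4 = 3 + 9/k, hence k = 9. Poisson regression with robust standard errors:

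| Log-rate slope per year of age | Active only, age band adjusted | Mean rate ratio per SD of log(mg/kg) | Arm-by-nominal-dose interaction |
|---|---|---|---|
| 0 | 7% | 1.00 | 7% |
| 0.03 | 11% | 0.96 | 5% |
| 0.05 | 21% | 0.94 | 6% |
| 0.08 | 40% | 0.90 | 5% |

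Without the age-band term the active-only test stayed at 5-7%. In this set-up the dose step at 12 offsets weight gain across bands, so the bias depends on the assumed dosing structure.

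**4. Adding baseline frequency, with weight prognostic.** The plan adjusts for baseline frequency and admits only children with 2-6 run-in attacks, so both were added. Numbers per trial come from 226 evaluable at 2:1: 226 × 2/3 ≈ 151 active and 75 placebo. Weight acts on both run-in and outcome rates. Three sets of runs differ in assumptions such as the weight curve and the pre-treatment rate. Sets A and B used 1,000 runs per setting; B was not run at zero.

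| Attacks per 10 kg | Set A | Set B | Set C |
|---|---|---|---|
| 0% | 7% | - | 7% |
| +5% | 10% | 7% | 10% |
| +10% | 21% | 15% | 19% |
| +15% | 35% | 26% | 32% |

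The interaction rejected in 6-7% (A) and 6-8% (C) at every slope. Simulation error at 5% with 1,000 runs is √(0.05 × 0.95/1000) ≈ 0.7 points. The small excess at zero slope is shared by both methods. Without the baseline count, set A gave 6%, 11%, 24% and 41%, so baseline adjustment helps only modestly: one four-week count is a noisy measure of a child's underlying rate.

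**5. Placebo children entered at zero dose.** The arm term then absorbs the active-placebo contrast, and the dose slope still comes essentially from treated children. Set A gave 6%, 9%, 21% and 34%.

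**The case against.** The strongest reply is that this is one sentence in a condensed article about one secondary analysis, and that covariates for such an analysis are commonly left to the SAP, which is not shown. That stands as a limit: a fuller document may already deal with it. But the article does not leave the terms open. It lists them, and following the list gives a confounded test.

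Several stronger readings are tempting and are not supported:

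- A reader might infer that the slope reflects only who the child is. A real dose effect would also enter it; the two cannot be separated.
- A reader might infer that nothing is adjusted. Age band and baseline frequency are in the plan and reduce the bias.
- A reader might infer that the plan states an active-only analysis. It refers to dose of the active treatments, but also to an arm term and the full analysis set. Step 5 shows that this hardly matters.
- A reader might add dose reductions for side effects as a further source of bias. The article describes none.
- A reader might take the interaction as a clean test of dose. It is not. In an illustration with no dose effect but a treatment effect varying by 15% per 10 kg, it rejected in 17% of runs. It also costs power: 36% against 68% for the active-only slope, for a true 15% fewer attacks per SD.

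It is also fair that nothing in the article says heavier or older children have more attacks. With no such link, the planned test is close to nominal.

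**Conclusion.** The point holds in a limited form. As written, the analysis yields an observational association that cannot carry the test named in the secondary hypotheses, because dose is not randomised and weight, formulation and age within band are not listed for adjustment. Under the step 4 assumptions, false rejection is about 7% with no weight link, 7-10% at 5% per 10 kg, 15-21% at 10% and 26-35% at 15%, against 6-8% for the interaction. These are illustrations: the weight curve, the prognostic slopes and the dose step are assumed. What does not depend on them is the structure, which follows from age-specific doses and self-chosen formulation. The primary comparison of each drug with placebo is untouched.

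**What to change.** - Derive the planned nominal mg/kg/day for every child, placebo included, from the assigned tablets or volume and baseline weight. Matched tablet numbers and volumes make this possible for placebo children, using the active drug of the trial they belong to.
- In each trial's Poisson model, test the arm-by-nominal-dose interaction. Include arm, nominal dose, weight, continuous age, formulation and baseline frequency as main effects, beside the terms already listed. The nominal-dose main effect will be nearly collinear with the others, which is harmless because it is not interpreted.
- Report the association within treated children as descriptive.
- Label the result exploratory and non-randomised, since the interaction cannot separate dose from a treatment effect that varies with age or weight.
- State the window meant by the period in the analysis sentence. It follows a list that includes weeks 25-28 and 37-40, which fall after the treatment phase.

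The cost is one derived variable and some wording. Weight is already measured at baseline, and assigned formulation and quantity are known. The real price is lower power than the active-only slope.
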